**Figure 1 F1:**
[figure not shown]
Design of the study using MRC complex intervention framework, inclusive of time schedule for various phases.

The RCT comprises an exploratory trial, to complete the modelling and piloting phase of the MRC 4-phased framework [26]. The RCT employs a 2 by 2 factorial design, as illustrated by Figure 2. The factorial design gives the RCT 4 arms: 3 treatment conditions (covering: psychoeducation alone; peer support alone; and combined psychoeducation and peer support) and a control condition. This design is chosen to fit with the two active components in the intervention, i.e. psychoeducation and peer support. Considering that these two ingredients may work independently as well as inter-dependently, the three treatment arms allow an investigation not only to determine the effectiveness of the combined psychoeducation and peer-support treatment condition, but also of how each ingredient impacts independently on particular participants’ outcomes, minimising any contamination [26,27]. Hence, the factorial design RCT will aid our theoretical understanding of the intervention, how it works, how its ingredients interact with each other and ultimately how it supports changes in the targeted outcomes. Furthermore, the results using the factorial design will inform the optimal intervention to be used in the full scale trial.

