#### Outcome data collection

Assessment of participants is conducted through completion of online questionnaires for demographic data and outcome measures at baseline (T1=week 0); at end of intervention (T2=week 10) and at 10-week follow-up (T3=week 20). Such data is collected directly from the participants via online survey tool inbuilt within the trial.

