### Analysis

#### Quantitative data

Ordinal outcome data collected at baseline (T1), post-intervention (T2) and 10 week-follow up (T3) will be transferred into ranked scores, ready for analysis. Descriptive statistics focusing on variance and confidence interval estimation will then be performed. A variety of tests will be employed to compare within and between subjects, for example: Mann–Whitney and Wilcoxon Tests. Also ANOVA will be performed on ranked data. Following the framework and its elements for optimising trial parameters [27], the trial analysis will also provide data for calculating sample size and the effect size estimate for a future definitive trial. All analyses will be carried out using SPSS (SPSS, Inc.; Chicago, Illinois).

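### The named analyses commit to no baseline-adjusted comparison between arms and to no main-effect or interaction terms, although the 2x2 design was chosen for those effects

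*Protocol article*

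**What the plan says.** The Methods section (paragraph after Figure 1) sets the design: "The RCT employs a 2 by 2 factorial design, as illustrated by Figure 2". It gives the reason too. Besides the combined condition, the trial should show the separate effect of each component, "but also of how each ingredient impacts independently on particular participants’ outcomes, minimising any contamination", and it should show "how its ingredients interact with each other and ultimately how it supports changes in the targeted outcomes".

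Under Outcome data collection, all participants are assessed at week 0 (T1), week 10 (T2) and week 20 (T3). A baseline value of every outcome, including the primary outcome WEMWBS, is therefore scheduled.

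The Quantitative data section then names the methods. First, "Ordinal outcome data collected at baseline (T1), post-intervention (T2) and 10 week-follow up (T3) will be transferred into ranked scores". Next come descriptive statistics with variances and confidence intervals. Then: "A variety of tests will be employed to compare within and between subjects, for example: Mann–Whitney and Wilcoxon Tests". Last: "Also ANOVA will be performed on ranked data". The factors, covariates and time structure of the ANOVA are not given. The section ends by saying that the results will supply the effect size and sample size for a definitive trial.

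The Sample size section disclaims hypothesis testing and treats 30 analysable participants per arm as enough to estimate outcomes and an effect size.

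**The concern.** The design paragraph and the analysis paragraph do not meet. The first asks for two component effects and their interaction. The second names methods without tying any of them to the two factors. A Mann–Whitney test compares two groups and cannot estimate an interaction. A paired Wilcoxon test uses the baseline, but only within a group, so it does not sharpen a contrast between arms. An ANOVA on ranks could carry the factors and a covariate, but nothing in the text says that it will.

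The T1 score is normally the strongest available predictor of the follow-up score, and it costs nothing further to use. Leaving it out of the between-arm comparison widens the interval around every effect. That matters here because estimates are what the trial is meant to produce. Ranking adds a second difficulty: an effect on ranks is not in WEMWBS points, and an interaction on ranks need not match one on the raw scale.

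**Working it through.** **Inputs from the article.** Four equal arms; 30 analysable per arm (Sample size); outcomes at T1, T2 and T3 (Outcome data collection).

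**Assumed input.** The correlation r between baseline and follow-up score is not in the article. It is shown at 0.3 and from 0.5 to 0.7.

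**The plan's own figures.** The article states no precision or power figure to reproduce. Its 144 follows from 120 × 1.2, or 36 per arm. After a full 20% loss, 36 × 0.8 = 28.8 per arm would remain. Using 28.8 instead of 30 moves the two unadjusted half-widths below only from 0.51 to 0.52 and from 0.36 to 0.37, so 30 is used throughout.

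**Unadjusted 95% half-widths, in SD units, n = 30 per arm.**
- One arm against another, such as combined against control: 1.96 × √(2/30) = 1.96 × 0.258 = 0.51.
- 2x2 margin, 60 with a component against 60 without it: 1.96 × √(2/60) = 1.96 × 0.183 = 0.36. The variance is half that of the pairwise contrast.
- Interaction, a difference of two differences: 1.96 × √(4/30) = 1.96 × 0.365 = 0.72.

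**Baseline adjustment.** It multiplies the variance of any of these contrasts by 1 − r², and the width by √(1 − r²).

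| r | variance factor | width factor | pairwise half-width | margin half-width |
|---|---|---|---|---|
| 0.3 | 0.91 | 0.95 | 0.48 | 0.34 |
| 0.5 | 0.75 | 0.87 | 0.44 | 0.31 |
| 0.6 | 0.64 | 0.80 | 0.41 | 0.29 |
| 0.7 | 0.51 | 0.71 | 0.36 | 0.26 |

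Baseline adjustment alone therefore saves 25% to 49% of variance for r from 0.5 to 0.7, which is 13% to 29% of interval width. At r = 0.3 it saves about 9% of variance.

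**Both changes together.** Measured against an unadjusted pairwise comparison, the variance factor is (1 − r²)/2, or 0.375, 0.32 and 0.255 at r = 0.5, 0.6 and 0.7. The half-width falls from 0.51 to 0.31, 0.29 and 0.26.

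**Does the gain survive ranking?** A simulation of 3,000 trials per value of r used 30 per arm, an assumed effect of 0.5 SD for one component and no interaction. A 2x2 ANOVA on ranks detected the effect in 74% to 76% of runs. The same model with ranked baseline as covariate did so in 86% to 95% for r from 0.5 to 0.7. Power is not this trial's aim; the comparison only shows that the baseline carries information on the rank scale too.

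**What the margin means under interaction.** Suppose a component adds 0.5 SD when given alone and the interaction is −0.5 SD. The margin is then 0.5 − 0.5/2 = 0.25 SD, half of the component's effect when given alone.

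**The case against.** The strongest reply is that the text leaves the model open. The tests are introduced as examples, and T1 scores are among those ranked for analysis. Wilcoxon tests use the baseline within subject, and the ANOVA might be 2x2 or repeated-measures. Even a Mann–Whitney test could compare all who received psychoeducation with all who did not, 60 against 60. An article may leave such detail to a fuller plan, and in a pilot that disclaims hypothesis testing the result is a wider interval, not a wrong conclusion.

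Most of this stands. A reader might infer that the plan ignores both the baseline and the factorial structure and so gives up about half of its precision. The article does not support that. It does not say which groups the two-group tests compare or which terms the ANOVA contains. Halving the variance through the margin presupposes that the estimate would otherwise be an unadjusted 30 against 30. If the ANOVA is already 2x2, only the baseline part of the loss remains. The Methods section also expects the two components to work inter-dependently, so the margin cannot be assumed to be the effect of a component alone.

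The reply does not remove the point. The article did choose to name its methods, and none of those named is a baseline-adjusted comparison between arms or is linked to the effects that justify the design. A better method exists for data already scheduled.

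**Conclusion.** The point holds as a failure to commit. The Quantitative data section fixes on rank tests and an ANOVA on ranks without baseline adjustment of any between-arm comparison and without main-effect or interaction terms, although the Methods section rests the design on those effects.

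The saving that does not depend on how the ANOVA is built around the factors is the one from baseline adjustment: 25% to 49% of variance for an assumed r of 0.5 to 0.7, and about 9% at r = 0.3, provided that the ANOVA carries no baseline term. The fall in half-width from 0.51 to between 0.31 and 0.26 SD needs two further conditions: that the plan's estimate would be pairwise and unadjusted, and that the margin is the quantity wanted. Contrasts between single arms gain only from the baseline. The interaction stays imprecise in any analysis of this sample.

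The change is worth making because it costs little. Without it the intervals are wider than they need be and the factorial question has no stated analysis. The trial's validity is not at risk.

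**What to change.** Name one main analysis in the Quantitative data section: raw WEMWBS at T2 and T3, modelled on T1 WEMWBS, psychoeducation, peer support and their product. Use either a mixed model with treatment-by-time terms, so that week 10 and week 20 effects stay separate, or an ANCOVA at each time point.

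Code each component as −1/2 and +1/2. The component coefficients are then the margins and the product coefficient is the difference of differences. With 0/1 coding and a product term, the component coefficients would be effects against control alone, with the pairwise half-width of 0.51 SD.

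Report for each time point, with 95% confidence intervals:
- the two main effects;
- the interaction, described as imprecise (half-width about 0.72 SD before adjustment);
- the simple effects, including combined against control (0.51 SD before adjustment).

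State that a main effect is read as a component's own effect only if the interaction appears small, and that an interval this wide cannot establish that it is. Use the same model for the secondary scores and keep the rank tests as sensitivity analyses.

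The cost is analysis wording. No participants, assessments or measures are added.

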#### Qualitative data

The qualitative data on participants’ experiences and perceived acceptability of the intervention will be analysed using Ritchie et al’s thematic analysis framework [39], assisted by NVivo (http://www.qsrinternational.com). This method of analysis is chosen because it is suited to the analysis of large qualitative data sets and enable feedback to the participants. Thematic analysis using Ritchie et al’s framework [39] will classify and organise data according to key themes and concepts. Three broad stages are involved in the analytical process. First, initial themes are identified by “indexing” transcript. These themes will then guide formation of a framework within which transcribed material is summarised. Key categories are then identified to help described the data. Finally, patterns of association are explored and explained. To ensure our analysis is grounded in the data, it will be performed in parallel to the qualitative data collection, so the developing themes and framework of analysis can be tested and validated in latter data [33,39]. The data-analysis will be complete when “saturation” of themes is reached. We estimate that about 15 interviews will be needed though the guiding principle of saturation will take precedence in determining the completeness of the qualitative analysis [33,39].

## Discussion

The design of the intervention is based upon the stress-appraisal and coping theory [14] that is commonly used in conventional psychoeducational interventions targeting family members and relatives (for example: [12,13]). The needs for information and peer support have been identified by siblings themselves as well as in a prior qualitative study targeting the same population group [9,15]. As such, some conventional outcome measures like the ECI [31] and the Assessment of Perceived General Self-efficacy [30], together with more recent development, like the MAKS [29] and WEMWBS [28], are used in this trial. Whilst retaining some frequently used outcome measures targeting changes in knowledge and self-efficacy, we have decided against including some other traditional outcome measures that have been used historically to determine changes in family members’ perceived burden and expressed emotion [12,13]. Our earlier research on siblings’ experiences and needs of service identified that most of them do not regard themselves as (primary) “carers” [9,15]. Instead, most siblings see their parents shouldering the primary carer role and their own contribution being supporting their ill brother or sister as well as their parents.

Considering the dearth of research with siblings of people with FEP, this trial serves as an exploratory study which has, as one of its aims, to produce an estimate of the value of outcomes. On a more general level, the trial will test out the feasibility and efficacy of an innovative intervention delivered online, which draws its theoretical base from well researched psychoeducation and peer support which is conventionally delivered face-to-face. Considered together with data on usage patterns (e.g. number of hits, frequency and duration of use) which is inbuilt within the online medium and is collected as a matter of routine, further analysis could be conducted on feasibility and correlation between efficacy and usage.

The online delivery process of the intervention arguable provides further benefits in enhancing the qualities of the randomisation, concealment (to participants) and double blinding (to both the participants and the researchers) as all procedures are pre-set by the CTU and IT technicians, independent of the research team who is responsible for data analysis. Data collection is direct from the participants to the online outcome measure tools, to minimise any possible contamination brought about by a researcher interviewing the participants.

The intervention developed through the E-Sibling Project has the potential to be disseminated widely at minimal cost given its online design and delivery medium, in the medium term future. The intervention will provide a service to siblings who are currently often invisible to the statutory service and voluntary organisations providing a service for carers.

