### Design

#### Randomisation, treatment allocation and blinding

This is a factorial design RCT in which participants are randomised and allocated to 4 conditions: 3 treatment conditions in addition to treatment as usual (control). The three treatment arms will allocate participants into either: psychoeducation alone; peer support alone; or combined psychoeducation and peer support. Screening for eligible participants against inclusion and exclusion criteria is conducted online through screening questionnaires. All eligible participants will then be allocated to one of the three treatment or the control condition. Randomisation is done using computer-generated permuted blocks and is carried out by an independent Clinical Trial Unit (CTU) to ensure blindness. Eligible participants will receive a computer-generated account with username and a unique password as well as the treatment group they have been allocated to.

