#### Outcome measures

Sibling-participants will be assessed on the primary outcome and three further secondary outcomes at three time-points. Data collection using the following outcome measures tools is through online completion by all participants across the treatment and control conditions.

The primary outcome of this intervention is siblings’ mental wellbeing measured by a self-administered tool, the Warwick-Edinburgh Mental Wellbeing Scale (WEMWBS) [28]. WEMWBS has been validated to assess the impact of interventions on the mental wellbeing of a population sample [28]. Its brevity of 14 positively-worded items and 5 response categories make it ideal for use in this trial.

There are three secondary outcome measures, including: knowledge of mental health using Mental Health Knowledge Schedule (MAKS) [29]; self efficacy using the Assessment of Perceived General Self-Efficacy (APGSE) [30], and negative and positive experience of caring using Experience of Caregiving Index (ECI) [31].

The intervention, especially its psychoeducation component, is expected to impact on participants’ knowledge about psychosis. The MAKS is an ideal tool to assess and track stigma-related mental health knowledge amongst the sibling-participants. It has been validated for use in both face to face interviews and for online data collection [29]. To assess participants’ perceived self-efficacy with regard to optimistic beliefs about coping with a large variety of stressors, regardless of their circumstances, the online version of the APGSE [30] is used. This version, with a 10-item scale, has been found to be valid and feasible for online use. Finally, for assessing the sibling-participants’ experiences of caregiving, the ECI [31] will gather relevant information from siblings. The ECI contains 66 items covering 10 sub-scales of both positive and negative experiences of caregiving. In this trial, all 10 sub-scales inclusive of further break-down questions will be presented in a format of brief statements to the participants via an online questionnaire. The 10 sub-scales are: effects on family; stigma; negative symptoms; difficult behaviour; dependency; loss; positive personal experiences; and good aspects of the relationship with the service users; problems with services; and need for back up.

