#### Process evaluation

Data on patterns of uptake and usage (number of hits, time spent on-line etc.) from all participants will be monitored to correlate efficacy with usage and to ascertain feasibility.

After completion of the follow-up questionnaire data (T3=week 20), about 20% of the participants (n=20) across the three treatment groups will be purposively selected for interview to explore their experiences of using the resource and the perceived acceptability of the intervention. Purposive selection is used to identify the participants to ensure representation of diverse experiences and views from those with ethnic minority backgrounds, frequent and infrequent users whose experiences may impact on their usage and outcomes. Conventional delivery of psychosocial interventions (i.e. face to face) is known to be less likely to be offered to or accessed by people with Black and Minority Ethnic backgrounds (BME) [7]. The purposive sampling for the process evaluation aims to investigate if the online delivery and medium addresses this well-known access and equality issue, in addition to seek to understand their experience and perceived acceptability of the intervention. A post-intervention individual semi-structured interview will be conducted in person, via phone or online conference, depending on the participants’ preference. In addition, data on patterns of uptake and usage from all participants, e.g. number of hits and time spent on the treatment condition allocated will be monitored to correlate effectiveness with usage and to ascertain feasibility.

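### The article claims double blinding, but participants are told their allocated group and can see what their arm contains, so the self-rated outcomes are not blinded

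*Protocol article*

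**What the plan says.** The Discussion of the protocol article lists blinding among the advantages of the online format: "enhancing the qualities of the randomisation, concealment (to participants) and double blinding (to both the participants and the researchers"). The reason it gives is "as all procedures are pre-set by the CTU and IT technicians, independent of the research team who is responsible for data analysis".

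The section on randomisation, treatment allocation and blinding says that randomisation is "carried out by an independent Clinical Trial Unit (CTU) to ensure blindness". It then says that eligible participants receive an account with a username and "a unique password as well as the treatment group they have been allocated to".

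Under Outcome measures, the primary outcome is "mental wellbeing measured by a self-administered tool, the Warwick-Edinburgh Mental Wellbeing Scale (WEMWBS"). The three secondary instruments are likewise completed online by participants in every arm. On the data route, Outcome data collection says "Such data is collected directly from the participants via online survey tool inbuilt within the trial", and the Discussion repeats the point: "Data collection is direct from the participants to the online outcome measure tools".

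The section on design and content of the intervention describes peer support as a closed, moderated online forum. The Control condition section describes a mock-up on the same website, made up of factsheets.

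**The concern.** A trial that tells participants their group cannot also blind them to it. This matters more than usual here because no independent assessor rates anything. The participant is the outcome assessor for mental wellbeing, knowledge, self-efficacy and experience of caregiving. A participant who knows that they have the combined package, or only the factsheets, may answer a wellbeing scale differently for that reason alone. Effort and dropout may also differ.

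The main quantitative product of the trial is an effect estimate for a definitive study, as the Sample size and Quantitative data sections say. A reader who is told that the trial is double blind would see no reason to allow for expectation effects in that estimate.

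**Working it through.** The point involves no power, standard deviation or sample size, so there is no figure to reproduce. The check sets the statements side by side.

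1. **Are participants blinded?** The Discussion says yes. The randomisation section says that they receive their treatment group with their login. If they know the group, they are not blinded, so the two places contradict each other.

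2. **Could the disclosure be harmless?** The text says that the group is sent; it does not say in what form. A neutral code is conceivable, though none is described. Even with a code, a participant in either peer support arm finds a moderated forum, and a control participant finds factsheets. Someone who has read the trial information could largely work out the condition from what is on the screen.

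3. **Does the stated reason support the claim?** The reason is that the trials unit and IT technicians fix the procedures in advance, independently of the analysing team. Taking each property in turn:
   - Allocation concealment (nobody can foresee or steer the next assignment): supported.
   - Blinding of the analysis team: possibly supported, if that team receives coded arms.
   - Blinding of participants: not supported. Who generates the sequence has no bearing on what participants are told or shown.

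4. **Does direct online data collection repair it?** It removes the influence of an interviewer. It does not remove the respondent's own expectations, and the respondent is the only rater.

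5. **Reach.** All four arms (144 participants planned), all four instruments, and both assessments after baseline (week 10 and week 20).

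**The case against.** The strongest reply is that this is an exploratory trial which disclaims hypothesis testing, that the blinding sentence stands in the Discussion and is softened by its wording, and that no sample size or analysis method depends on it. The design also has real masking features: a mock-up control on the same website, and the same usage advice, weekly reminders and support centre for all four conditions. These may narrow differences in expectation.

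Much of this stands. It makes the point a correction and a stated limitation rather than a fatal flaw. It does not remove the contradiction, and an exploratory trial whose estimates feed a later design still has to say how those estimates might be biased.

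Three stronger readings are tempting, and the document does not support them:

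- **That researcher blinding fails too.** A reader might infer this because interviewees "across the three treatment groups will be purposively selected for interview to explore their experiences of using the resource". Whoever selects them must know that they are not controls. But the Process evaluation section does not say who selects, and it places selection after the follow-up questionnaires without saying whether that means each person's own or everyone's. It does not show that the analysis team learns allocations, or that anyone does before the last outcomes are in.
- **That baseline is answered after the group is known.** A reader might infer this from the order of screening, allocation and account. The text labels T1 as week 0 baseline but does not place it relative to disclosure, and the participant flow is in a figure that is not available here.
- **That the bias has a known size.** The document gives no standard deviation and no expected effect. If one assumed a reporting shift of 0.1 to 0.3 SD and a true effect of 0.3 to 0.6 SD, the ratio would run from 0.1/0.6 (about 17%) to 0.3/0.3 (100%). That range is too wide to be informative and rests wholly on the assumptions.

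**Conclusion.** The claim of participant blinding is wrong as written. It contradicts the article's own account of what participants receive, and the visible difference between arms would undermine it in any case. The self-administered primary outcome and the three self-reported secondary outcomes are therefore assessed with knowledge of allocation, or a good guess at it. Allocation concealment is credible, and blinding of the analysis team remains possible.

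The size and even the presence of bias cannot be established from the document. The conclusion is that the protection claimed is absent, not that the estimates are shown to be inflated. It rests on reading the disclosure in its ordinary sense, that participants learn their condition; if only a code is sent, the argument from visible content still applies. This should be fixed, but it does not threaten the feasibility aims.

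**What to change.** 1. In the randomisation section and in the Discussion, replace the double-blinding claim with a statement of who is and is not blinded: allocation is concealed through the independent trials unit; participants are not blinded; the analysis team works on coded arm labels. In the randomisation section, give concealment, not blindness, as the purpose of independent randomisation.
2. State in the Discussion that, because participants rate every outcome, expectation bias is a possible limitation of the effect estimates carried into the definitive trial.
3. Issue accounts without the group label, under one neutral site name, and let the login open the content of the arm. This reduces the bias but does not remove it, because the content remains visible.

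The cost is a few sentences, a changed account message and a site setting. No participants, assessments or recruitment time are added, and the analysis is unchanged apart from coded arm labels.
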